## Aims and Objectives

The aim of the MAGPIE study is to explore differences in gut microbiota and metabolic correlates between trial intervention arms (feed rate, lactoferrin) and dynamic changes in the period preceding disease onset (NEC or LOS). We aim to determine effects in both the stool and urinary metabolome, because these may reflect changes in either bacterial or host metabolism, or both. Specifically, we will determine changes in the bacterial community and overall metabolome profiles using both LCMS and GCMS, and using computational tools will determine correlations between the microbiome such as predicted gene orthologs and resulting metabolite compounds. Our specific aims are to test the following hypotheses:
Trial interventions will result in detectable differences in gut microbiota that will be directly related to metabolic function;Infants who develop NEC or LOS will have differences in gut microbiota and metabolic profile in the period preceding disease onset compared to control infants;There will be detectable differences in gut tissue inflammatory response between surgically resected gut tissue affected by NEC and control tissue.

We will achieve these aims by determining the following outcomes:
Gut microbial diversity (e.g., Shannon Diversity Index) and differences in the proportions of key bacterial taxa measured using 16S next-generation sequencing in stool samples collected after enrollment on days 1–3, 7, 10–14, and 21 (±1) days.The association between gut microbiota and the stool metabolome using mixed-effect models, structural equation modeling (SEM), and ordination analyses. Stool metabolome is measured using GCMS and/or LCMS in samples collected on days 1–3, 7, 10–14, and 21 (±1) days.Pattern of gut microbiota prior to the onset of NEC or LOS measured using up to seven daily stool samples in the period immediately prior to disease compared to samples from control cases who do not develop disease.The gut tissue inflammatory response in surgically resected gut tissue affected by NEC and in control tissue (either non-affected tissue from the same infant or tissue from an infant requiring gut resection who does not have disease) will be determined by immunohistochemistry. This will be measured after trial completion by retrieving samples from hospital pathology archives.

Our analytical models will also explore the effects of clinical risk factors for NEC and LOS such as gestation and markers of illness severity, and the effects of exposure to interventions such as breast milk and antibiotics, and consider other key outcomes such as time to full feeds, age at discharge, and growth, e.g., predischarge weight gain.

## Procedures—Summary

We will
Recruit at least 480 infants from up to 10 neonatal units in the UK enrolling infants to ELFIN.Identify stored samples from infants recruited to SIFT (one site only).Collect a daily stool and urine sample from MAGPIE infants until hospital discharge (average duration 40–50 days) or transfer back to local neonatal unit.Retrieve any residual resected gut tissue of enrolled infants who undergo intestinal surgery.Identify samples which are the most:
*informative*—based on trial intervention and disease presence;*comprehensive*—consistency of daily sampling;*representative*—balanced for trial intervention and other key factors, e.g., gestation, breast milk exposure.Samples to be analyzed will include
*all diseased cases*: infants who meet the SIFT and ELFIN internationally agreed predefined case definitions of confirmed NEC or LOS following review at Blinded Endpoint Review Committee;*non-disease cases*: infants who do not develop NEC or LOS, selected using matching algorithms to ensure trial intervention and risk factor coverage.The samples analyzed will focus on the early postnatal period when trial intervention differences will be greatest: e.g., day 0—3, 6–8, 9–11, 13–15, and 20–22 in ~25–50 infants per trial intervention arm. While we aim for daily sampling we recognize this will not always be achieved due to the complexity of the NICU working environment, combined with the fact that many sick infants do not pass a stool every day. We will also analyze samples at additional time points as necessary to ensure a daily sample is analyzed for up to 7 days before diagnosis in all diseased cases and match these to non-disease controls.Analyze samples for
*gut microbiota* using next-generation sequencing on the MiSeq (Illumina) platform to determine gut microbial patterns;*stool VOC* using “headspace” GCMS;*stool metabolomic profile* using LCMS to determine patterns in the metabolome;*urine metabolomic profile* using LCMS and assays for inflammatory proteins, e.g., intestinal fatty acid-binding protein (iFABP) where sufficient samples and informative cases exist.Determine changes due to trial interventions and changes preceding disease onset. We will explore dynamic changes in the gut community structure: proportions of key bacterial operational taxonomy units, presence of specific pathogenic strains, diversity, richness, and stability of communities.Analyze resected gut tissue using optimized immunohistochemistry to determine gut immune response where NEC develops. If sufficient samples exist, explore how trial interventions (feed rate, lactoferrin) and changes in gut microbiota or metabolome may relate to histological findings.Store residual samples in a Human Tissue Act (UK) and research ethics approved Newcastle University Biomedicine Biobank (the “Great North Neonatal Biobank”) for use in future studies.^4^ HTA license no. 12534, Ethics approval 15/NE/0334, IRAS 161883.

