### Enrollment, Consent, and Data Collection

Parents can be approached for written informed consent at any time after enrollment to ELFIN is complete, but this will usually be within the first 3 days, and frequently will occur at the same time as consent to ELFIN. Written information will explicitly state the intention to share and use data collected for ELFIN. Research ethics approval allows the collection of stool and urine samples and storage on the NICU prior to signed consent for MAGPIE, but any such samples will be destroyed if consent is not obtained. We will use data collected for SIFT and ELFIN by electronic encrypted data transfer from the clinical trials unit (NPEU) and supplement this with additional items for MAGPIE that include specific antibiotic type, use of prophylactic antifungal and probiotic strain/brand if these are used, and date and time of stool and urine collection.

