#### Necrotizing Enterocolitis

Necrotizing enterocolitis may be diagnosed at surgery, at postmortem or clinically and radiologically: at least one of the following clinical signs present: bilious gastric aspirate or emesis, abdominal distension, or occult or gross blood in stool AND at least one of the following radiological features: pneumatosis intestinalis, hepatobiliary gas, or pneumoperitoneum. Infants who satisfy the definition of NEC but at surgery or postmortem have a “focal gastrointestinal perforation” will not be coded as having NEC.

All diseased cases meeting the predefined case definition of NEC or LOS will have samples analyzed (expected total ~70–100 infants). Samples from up to 200 non-diseased cases will be selected to ensure sufficient coverage of intervention arms using matching algorithms and coverage of other clinical risk factors and outcomes. We will also analyze samples from non-diseased cases to determine microbiomic and metabolomic profiles between trials arms.

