
### Statistical Analysis

There are three major modeling issues that have to be addressed in this analytical pathway:
(i)the multivariate nature of the microbiome and metabolome, and data generated from immunohistochemistry;(ii)the longitudinal/developmental component in the neonate, which will lead to repeated measures of disease state and microbiome on the same individuals, and(iii)the interdependence and interactions between different predictors, which may have both direct and indirect effects on incidence and progression of disease.

The analytical approach used in this study will focus on modeling the relationship between putative risk factors, trial interventions, and incidence of NEC and LOS from longitudinal data capturing variation in both risk factors and disease through time, and the any differences in non-diseased cases between trial arms. We will use a progressive modeling strategy based on combining multivariate analyses of micro- and metabolomic immunological data, with mixed-effect modeling of outcome in relation to drivers of disease; and finally, mixed-effect SEM to quantify the importance of interacting factors and drivers. Specifically, we will
(i)quantify the impacts of individual risk factors in causing disease;(ii)quantify the effects of direct and indirect risk factors on disease;(iii)quantify the dynamics of pathogens, the neonatal microbiome, the immune response, and their impact on outcomes, and(iv)identify the impacts of trial interventions and clinical management on the drivers and disease.

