### Quantifying the Direct and Indirect Impact of Risk Factors on Disease

We will use repeated measure mixed-effect modeling to quantify the direct effects of microbiome on risk of disease while adjusting for clinical factors. We will use case as the random effect and adjust for autocorrelation in the response using appropriate correlation structures in the model. The applicants have used this approach extensively to investigate the epidemiology of food-borne pathogens (92). We will use an SEM approach to quantify direct and indirect effects of risk factors on the incidence of disease. We will develop a set of models that characterize the relationship between clinical factors, the changes in gut microbial community types, developmental stage (postnatal and postmenstrual age), and comorbidities associated with disease onset and then challenge the model with the data derived from the laboratory and clinical data collection (93).

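### Controls are selected on trial arm, gestation and breast milk exposure, yet the effects of these same factors on NEC/LOS are to be quantified, and nothing separates those models from the selected set

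*Protocol article*

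**What the plan says.** Under Procedures—Summary, the protocol article analyses every diseased infant, together with non-diseased infants "selected using matching algorithms to ensure trial intervention and risk factor coverage". The same list wants the analysed samples to be "balanced for trial intervention and other key factors, e.g., gestation, breast milk exposure", and also favours infants with consistent daily sampling. The Necrotizing Enterocolitis section gives the numbers: about 70–100 diseased infants, and "Samples from up to 200 non-diseased cases will be selected to ensure sufficient coverage of intervention arms using matching algorithms", plus coverage of other clinical risk factors and outcomes.

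The targets of estimation come later. Aims and Objectives says the models will also explore clinical risk factors, with gestation as an example, and exposures such as breast milk. Statistical Analysis will "quantify the impacts of individual risk factors in causing disease" and "identify the impacts of trial interventions and clinical management on the drivers and disease". The section on direct and indirect impact will use an SEM to "quantify direct and indirect effects of risk factors on the incidence of disease". Its mixed model has a random effect per infant, an autocorrelation structure and adjustment for clinical factors.

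Under Enrollment, Consent, and Data Collection: "We will use data collected for SIFT and ELFIN by electronic encrypted data transfer from the clinical trials unit".

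**The concern.** Arm, gestation and breast milk exposure help decide which non-diseased infants are assayed, and are also exposures whose effect on disease is to be quantified. If controls are made to resemble the cases on a factor, its association with disease is removed from the sample by design. If controls are spread evenly over its levels, the association is changed by however far that spread departs from the non-diseased cohort.

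Models without laboratory variables could be run in all enrolled infants. An SEM with paths through the microbiome cannot, because it needs assayed samples. The planned random effect, autocorrelation structure and covariate adjustment do not correct for selection that depends jointly on outcome and exposure.

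The stake is interpretation. A path from gestation or breast milk to disease that selection has flattened could be read as weak, or as explained by the microbiome, when the sampling produced it.

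**Working it through.** **Inputs from the protocol article.** 480 infants and 70–100 diseased (Sample Size Estimates); up to 200 controls (Necrotizing Enterocolitis); LOS 18% versus 13% (Overview of the SIFT and ELFIN Trials), used only to illustrate an arm effect. **Assumed:** size of the gestation effect, shape of the gestation distribution, 30% prevalence for a binary risk factor and its odds ratio, and the form of the matching rule.

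**1. The plan's case count.** NEC 5% and LOS 10%, independent: 480 × (1 − 0.95 × 0.90) = 69.6. NEC 5% and LOS 15%, no overlap: 480 × 0.20 = 96. The stated 70–100 fits its inputs, though these are ranges and allow other totals.

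**2. Case share.** Cohort: 70/480 = 14.6% to 100/480 = 20.8%. Selected set with 200 controls: 70/270 = 25.9% to 100/300 = 33.3%. This shifts intercepts and absolute risks. Over-sampling cases alone does not bias odds ratios for exposures not used in selection.

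**3. Arm.** With 240 infants per arm, cases number 240 × 0.18 = 43.2 and 240 × 0.13 = 31.2; non-cases 196.8 and 208.8. The cohort odds ratio is (31.2/208.8)/(43.2/196.8) = 0.68. With 200 controls:

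| Control selection | Controls, placebo : lactoferrin | Odds ratio |
|---|---|---|
| Random from non-cases | 97.0 : 103.0 | 0.68 |
| Balanced 1:1 by arm | 100 : 100 | (31.2/100)/(43.2/100) = 0.72 |
| Matched to cases by arm | 116.1 : 83.9 | 1.00 |

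**4. A binary risk factor with assumed prevalence 30%.** If controls are split 50:50 on the factor, the odds ratio in the selected set equals the odds of exposure among cases.

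| True odds ratio | Exposed among cases (risk 14.6%; 20.8%) | Odds ratio, 50:50 controls | Matched to cases |
|---|---|---|---|
| 2 | 43.4%; 42.2% | 0.77; 0.73 | 1.00 |
| 3 | 51.7%; 49.8% | 1.07; 0.99 | 1.00 |

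Even spread can therefore erase or reverse an effect when the factor is uncommon in the cohort.

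**5. Gestation, by simulation** (480 infants, all cases, up to 200 controls, unconditional logistic model).

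| Assumed OR 0.75 per week, arm 0.68 | Gestation | Arm |
|---|---|---|
| Matched on arm and gestation | 0.92 | 0.97 |
| Even spread over gestation-by-arm strata | 0.93 | 0.72 |
| Even spread, inverse-fraction weights | 0.75 | 0.69 |
| Balanced on arm only | 0.75 | — |

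Other assumed settings gave 0.90 to 0.94 for matching and 0.875 for even spread (true value 0.75), and 0.81 for even spread where the cohort value was 0.69. On the log scale, even spread keeps ln 0.93/ln 0.75 = 25%, ln 0.875/ln 0.75 = 46%, or ln 0.81/ln 0.69 = 57% of the effect. Matching keeps 22% (0.94) to 37% (0.90).

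With gestation per SD and nearest-gestation matching within arm (400 cohorts), the odds ratio fell from 2.24 to 1.18 and the arm odds ratio moved from 0.67 to 0.98. With 200 random controls the values were 2.27 and 0.66.

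**6. Microbiome exposure.** Under tight matching, a simulated microbiome odds ratio was preserved: 0.594 against 0.596.

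**The case against.** The strongest reply is that the article never specifies the matching rule. Coverage and balance may mean spreading non-diseased infants across arms and risk levels, not pairing them with cases. This stands in part. A reader might infer that the arm effect would vanish; that needs strict matching, and simple balance moves it only from 0.68 to 0.72. Balance on arm alone leaves gestation intact. But gestation and breast milk are named as balancing factors, and even spread over gestation also attenuated its effect. How far depends on the cohort: if gestation were already spread evenly among enrolled infants, little would change.

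Second, a reader might infer from the 26–33% case share that the study would report an inflated incidence. No section plans to report absolute incidence from the selected set; the models concern relationships with incidence.

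Third, the three hypotheses in Aims and Objectives concern arm differences in microbiota, pre-disease profiles and gut tissue. None is the effect of gestation or arm on NEC/LOS, and matching with adjustment suits the case-control microbiota contrast. This stands. ELFIN itself, with 2,200 infants, is the main source for the arm effect on LOS.

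Fourth, analysis sets and weights are commonly left to an analysis plan. That is fair for the models' details, and the article does not confine risk-factor models to assayed infants. It does not dispose of the point: the article itself fixes selection on these factors and names their effects as targets, and weights need sampling fractions recorded when infants are chosen.

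**Conclusion.** The point holds for the effects of the selection factors on NEC/LOS, if they are estimated unweighted in the laboratory-analysed set. Under the assumed effects, gestation loses roughly 63–78% of its log odds ratio when controls are matched to cases, and roughly 43–75% when they are spread evenly over gestation strata. The arm effect ranges from slightly changed (0.72) to nearly or wholly removed (0.97–1.00), depending on a rule the article does not state. Breast milk exposure was not simulated separately; the binary-factor table shows the mechanism.

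The exact sizes rest on the assumed gestation effect, gestation distribution and selection rule. The documents do not support a claim that the main microbiota hypotheses are compromised, or that odds ratios for exposures not used in selection are biased by over-sampling cases. The affected objectives are secondary and exploratory, so this is a should-fix, not a must-fix.

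**What to change.** 1. Estimate total effects of gestation, breast milk, other clinical factors and trial arm on NEC/LOS in all ~480 enrolled infants, from the trial data already to be transferred.
2. Select controls within defined strata with known, non-zero sampling fractions, and record them before assay. If completeness of sampling remains a criterion, build it into the strata.
3. In mixed models and SEMs that combine risk factors, microbiome and disease, weight by the inverse sampling fraction. With 200 controls the average control weight is (480 − 100)/200 = 1.90 to (480 − 70)/200 = 2.05, which restores the cohort case share.
4. Use conditional matched analyses only for exposures not matched on, such as microbiome and metabolome measures. They cannot recover the effect of a matching factor.
5. Make no claim about a selection factor's effect on disease from the unweighted set.

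The cost is one cohort model on data already held, record-keeping at selection, and somewhat wider intervals from weighting (not quantified here). No further infants or samples are needed. Strict matching without recorded fractions would rule out step 3, because some non-diseased infants could have no chance of selection.

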### Standard Operating Procedures (SOPs)—Sample Collection, Storage, and Transport

Samples will be collected, anonymized, and analyzed according to established SOPs already developed by members of the project team. In brief, stool samples are collected from the nappy/diaper using a clean disposable plastic spoon and placed in a glass pot with a lid. Samples will be collected at routine clinical nursing care times. Urine samples are collected according to standard NICU procedure, which typically involves collecting urine passed spontaneously onto sterile cotton wool ball, squeezed out using a sterile syringe, and aliquoted into two 2 ml cryovials. Samples are labeled and placed in a −20°C freezer (generally immediately or within an hour of collection) located on the NICU. Samples are then transferred frozen in batches from local hospitals to central laboratories where they will be stored at −80°C prior to microbiomic and metabolomic analyses. Transport of samples will take place every 6–8 weeks meaning the duration of local storage at −20°C is around 1–8 weeks, on average 3–4 weeks. We will record sample storage duration at −20 and −80°C and conduct analysis throughout the study period in a chronological fashion so that we can adjust, if required, for any confounding introduced by varying storage durations.

Short-term storage of stool samples does not significantly affect the microbial communities, although measurement of storage time of samples is important to avoid potential bias (73–75). We aim to account for the amount of time in storage for DNA extractions to minimize bias. To determine any storage effects, we will conduct quality control by comparing gold standard immediate DNA extracts from <10 samples to the same number following storage of stool for 12 and 18–24 months.

Any gut tissue resected during surgery for either NEC or other conditions (e.g., spontaneous intestinal perforation) will be retrieved from paraffin blocks located in NHS pathology archives after all clinical tests have been complete. Samples will be transported to the central laboratory for immunohistochemical analyses. It is possible that only 10–12 infants undergo surgery for NEC (or other conditions) and have residual tissue available. We will therefore consider the use of control tissue from other preterm infants available locally within one hospital (Newcastle Hospitals NHS Foundation Trust) where we have research ethics permission to analyze historical samples.

### Enrollment, Consent, and Data Collection

Parents can be approached for written informed consent at any time after enrollment to ELFIN is complete, but this will usually be within the first 3 days, and frequently will occur at the same time as consent to ELFIN. Written information will explicitly state the intention to share and use data collected for ELFIN. Research ethics approval allows the collection of stool and urine samples and storage on the NICU prior to signed consent for MAGPIE, but any such samples will be destroyed if consent is not obtained. We will use data collected for SIFT and ELFIN by electronic encrypted data transfer from the clinical trials unit (NPEU) and supplement this with additional items for MAGPIE that include specific antibiotic type, use of prophylactic antifungal and probiotic strain/brand if these are used, and date and time of stool and urine collection.

### Case Definitions of Disease (NEC or LOS)

We will use the internationally accepted definitions used by SIFT and ELFIN, which are subsequently confirmed at Blinded Endpoint Review Committees conducted by at least two senior clinician investigators blinded to trial interventions at the NPEU.

#### Late-Onset Sepsis

Microbiological culture of potentially pathogenic bacteria (including coagulase-negative staphylococci species but excluding probable skin contaminants) or fungi from fluid sampled aseptically more than 72 h after birth from blood or CSF, or clinically suspected sepsis (meeting three objective clinical criteria) AND intention for treatment for 5 or more days with intravenous antibiotics. If the infant died, was discharged, or was transferred prior to the completion of 5 days of intravenous antibiotics, this condition would still be met if the intention was to treat for 5 or more days.

